### **1.2.6 Endpoints**

As the main focus of this study is to evaluate the effects of sleep deprivation, all related parameters are considered as main endpoints.

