### 6.2 Pharmacodynamic endpoints

#### Part A

#### **Simulated and on the road driving**

- Standard deviation of lateral position (SDLP) (main parameter).
- Number of lane departures.
- Mean speed (MS).
- Standard deviation of speed (SDS).
- Perceived driving quality scale and perceived effort scale.
- Driving quality scale by driving instructor.
- Car driving exploratory biomarkers (drive safety score, head movements, steering wheel).

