### 7.1 Efficacy assessments

#### **On-the-road driving test**

Subjects will participate in validated on-road car driving tests. During these tests several safety precautions are taken to guarantee safety of the subjects and regular traffic. A licensed driving instructor (having access to dual controls) guards the safety of the subject and regular traffic during the test. In case the driving instructor or the subject is of the opinion that it is not safe to start or continue the driving test, the test will be interrupted. Subjects will operate a specially instrumented vehicle over a 55-km primary highway circuit, while maintaining a constant speed (95 km/h) and steady lateral position between the delineated boundaries of the right (slower) traffic lane. The subject will be allowed to deviate from this procedure only in order to overtake a slower vehicle traveling in the same traffic lane. The vehicle's speed and lateral position relative to the lane-lines is continuously recorded. These parameters are digitally sampled at 13 Hz by the MobilEye system (MobilEye Vision Technologies Ltd., Israel). Data is edited, off-line, to remove parts where data are disturbed by extraneous events (eg, passing maneuvers). SDLP (cm), ie, the weaving of the car, is the primary outcome variable. SDLP has been shown to be a sensitive measure to demonstrate dose-dependent differences from placebo for alcohol and psychoactive drugs including anxiolytics, antihistamines, antidepressants, hypnotics and analgesics, and drugs of abuse [4, 7, 25]. Standard Deviation of speed (SDS, km/h) will be a secondary variable. Mean lateral position (MLP, +/- cm), and mean speed (MS, km/h) are control variables. During screening, subjects will participate in a training driving test to become acquainted with the procedures of the driving test.

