#### Part A

Prematurely stopped on-the-road tests will only be included if more than 20 kilometres is driven, and only the last 10 kilometres will be used for data analysis.

The handling of missing, unused and spurious data will be documented in the study report.

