### 9.8.1 Prematurely discontinued on-the-road driving tests

Before and during the on-the-road driving test the subject and/or the driving instructor can stop the test prematurely for safety reasons. This will be noted as an event and the events will be summarized.

The number of subjects who did not finish the test will be summarized by:

1. Person who stopped the test (subject or driving instructor);
2. Amount of kilometres driven (rounded to 5km);

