## 9.9 Pharmacodynamics endpoints

The analysis of part A and part B will be done separately. The measurements of the afternoon after normal sleep will not be used for the primary analysis. The repeatability of the parameters measured during morning and during the afternoon after normal sleep will be assessed separately on the subset of the after normal sleep data.

The final analysis will be preceded by a data review which consists of individual graphs per visit by time of all pharmacodynamic measurements by time. The graphs will be used to detect outliers and measurements unsuitable for analysis.

The PD parameters will be listed by subject, group (sleep/sleep deprivation), visit and time. Individual graphs by visit/time will be generated.

All PD endpoints will be summarised (n, mean, SD, SEM, median, Min and Max values) by group (sleep/sleep deprivation), and will be presented graphically per group/time in bar graphs with standard deviation as error bars.

Parameters will initially be analysed without transformation, but if the data suggest otherwise, log-transformation may be applied. Log-transformed parameters will be back-transformed after analysis where the results may be interpreted as percentage change.

To estimate the differences between groups (sleep deprived/sleep) data will be analysed with a mixed model analysis of variance with fixed factor group and random factor subject. The contrast sleep vs sleep deprived will be calculated within the model.

To estimate inter- and intra-subject variability the subset data of the sleep group will be analysed with a mixed model analysis of variance with fixed factor time (morning/afternoon) and random factor subject. The variances will be estimated within the model.

The Kenward-Roger approximation will be used to estimate denominator degrees of freedom and model parameters will be estimated using the restricted maximum likelihood method.

Correlations of the change between sleep and sleep deprived values between the cognitive tests, simulated and on-the-road driving will be calculated.

The intra-subject variabilities will be reported as coefficient of variation (CV).

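### On-the-road lane departures are analysed as a raw count, but a stopped drive supplies only 10 km against up to 55 km for a completed one

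*Protocol*

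**What the plan says.** Four parts of the protocol bear on this.

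- **Section 9.4, Part A.** A prematurely stopped road test "will only be included if more than 20 kilometres is driven, and only the last 10 kilometres will be used for data analysis". The rule covers stopped tests as such and exempts no endpoint.
- **Section 7.1, On-the-road driving test.** "Subjects will operate a specially instrumented vehicle over a 55-km primary highway circuit". The only reduction for a completed drive is editing: "Data is edited, off-line, to remove parts where data are disturbed by extraneous events". There is no 10-km window for completed drives.
- **Section 6.2, Part A.** "Number of lane departures" is listed for simulated and road driving, as a count and not as a rate. SDLP is marked as the main parameter there, although section 1.2.6 says that "all related parameters are considered as main endpoints".
- **Section 9.9.** For the comparison of states, "data will be analysed with a mixed model analysis of variance with fixed factor group and random factor subject". There is no distance term or offset.

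Distance driven appears in the analysis sections only in the tabulation of stopped tests (the second section numbered 9.8.1), where it is rounded to 5 km.

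**The concern.** A count of lane departures grows with the distance over which it is taken. The window for stopped drives is harmless in this respect for SDLP, mean speed and SD of speed, because none of them accumulates with distance. Lane departures do accumulate. Taken together, the three rules set a count from 10 km beside a count from up to 55 km, often within the same subject, and nothing in the model corrects for the difference.

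Stops are made for safety, by the subject or the instructor (sections 7.1 and 7.2.1). If they occur more often after a night without sleep, the drives judged unsafe to continue receive artificially low counts. The sleep-deprivation effect on this endpoint then shrinks. Section 9.9 also plans correlations of change that include on-the-road driving. If lane departures are among the variables used, the same artefact would enter there.

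**Working it through.** **Plan's own figure.** The protocol gives no figure for lane departures. Its Part A design figure is power 0.80 for a 3.88 cm simulator SDLP difference (SD of differences 6.5 cm, 24 subjects, two-sided 0.05). The noncentral t with 23 degrees of freedom gives 0.7997, so that figure is correct. It has no bearing on this point.

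**Inputs from the protocol.** 10 km analysed per stopped drive (9.4), 55-km circuit (7.1), 24 subjects (9.3).

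**Assumed inputs.** The protocol gives no stop rate and no departure rate. I take k of 24 sleep-deprived drives stopped at random after 20 km (p = k/24), no rested drive stopped, and at first a constant departure rate with true ratio r.

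**Exposure share.** f = 10/55 = 0.182. If editing leaves 45 km of a completed drive (assumed), f = 10/45 = 0.222.

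**Attenuation of the raw count.** Observed ratio = r × (1 − (1 − f)p) = r × (1 − 0.818p). Share of the true mean difference retained = (observed ratio − 1)/(r − 1).

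| Stopped of 24 | Ratio, r = 2 | Difference kept, r = 1.5 | r = 2 | r = 3 |
|---|---|---|---|---|
| 1 | 1.93 | 90% | 93% | 95% |
| 2 | 1.86 | 80% | 86% | 90% |
| 4 | 1.73 | 59% | 73% | 80% |
| 6 | 1.59 | 39% | 59% | 69% |

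With f = 0.222 and r = 2 the ratios are 1.94, 1.87, 1.74 and 1.61, so editing hardly matters. A simulation with assumed departure rates (mean counts from 1 versus 2 up to 10 versus 20, 4 of 24 stopped at random) gave a raw ratio of 1.72 to 1.74, in line with the formula.

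**One subject.** A stopped sleep-deprived drive has expected count 10 × rate₁, and a completed rested drive 55 × rate₀. The expected change is a decrease unless rate₁/rate₀ exceeds 55/10 = 5.5.

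**Departures clustering before the stop.** Let the last 10 km have c times the drive's usual rate. The options for a stopped drive then give:

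- raw count: r(1 − p + 0.182cp). There is no attenuation only when 0.182c = 1, that is c = 5.5;
- rate from the last 10 km: r(1 − p + cp);
- rate from all D kilometres driven: r(1 − p + gp), with g = (D − 10 + 10c)/D.

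With r = 2 and 4 of 24 stopped (p = 1/6):

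| c | Raw count | Last-10-km rate | All km, D = 20 | All km, D = 40 |
|---|---|---|---|---|
| 1 | 1.73 | 2.00 | 2.00 | 2.00 |
| 1.5 | 1.76 | 2.17 | 2.08 | 2.04 |
| 2 | 1.79 | 2.33 | 2.17 | 2.08 |
| 3 | 1.85 | 2.67 | 2.33 | 2.17 |

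The raw count and the last-10-km rate are equally far from the truth when 1 − 0.182c = c − 1, so c = 2/1.182 = 1.69. For the all-kilometre rate, g − 1 = 10(c − 1)/D. Setting this equal to 1 − 0.182c gives c = 3/1.364 = 2.2 at D = 20 and c = 5/1.727 = 2.9 at D = 40.

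**Precision.** The Poisson standard error of a rate is proportional to 1/√km. Relative to 55 km it is √(55/10) ≈ 2.3 times as large from 10 km, and at most √(55/20) ≈ 1.7 times from all of a drive longer than 20 km, before editing.

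**The case against.** The best reply is that counting raw or per kilometre is a derivation detail. Section 9.1 leaves the derivation algorithms to the SAP, which is not shown and could convert the count to a rate. Section 7.1 does not list lane departures among the road-test variables, and the protocol does not define a road lane departure. Section 9.5 admits only data that can contribute meaningfully, section 9.9 provides a data review before analysis, and section 9.4 requires the handling to be reported. These clauses lower the chance that the mismatch goes unnoticed, but none of them prescribes scaling. The window, the count and the model terms are all stated in the protocol, and the conflict lies between those stated rules.

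The second reply is that every size above rests on assumed stop and departure rates. That stands. Drives stopped at or before 20 km are excluded, so only later stops matter, and if no included drive was stopped there is no bias of this kind.

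The third reply is that a per-kilometre rate can be worse than the raw count. For a rate from the last 10 km alone this stands: above c of about 1.69 it is further from the full-drive rate, in the direction that exaggerates the effect. Safety stops make such clustering plausible. This is why the fix below uses the whole analysable drive.

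A reader might infer that the 10-km rule biases the road-driving results in general, SDLP included, or that the lane-departure effect is known to be underestimated. The documents support neither. SDLP, mean speed and SD of speed do not scale with distance, and nothing is said about how often, or in which state, drives stop. Nor do the documents say that lane departures will enter the planned correlations.

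**Conclusion.** The point holds as a minor one. As written, a road drive stopped after more than 20 km enters the lane-departure count with about 18% of full exposure (22% if 45 km remain usable, assumed), and the section 9.9 model does not adjust for it. If such stops are more frequent after sleep deprivation, the effect on this endpoint is pulled toward zero, unless the rate in the last 10 km is about 5.5 times the full-drive average. With a constant rate and a true ratio of 2, between 1 and 6 stopped drives of 24 would leave 93% down to 59% of the true mean difference.

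The exposure mismatch and the missing distance term rest on the protocol alone. The direction and size of the bias rest on assumed stopping and departure rates. One endpoint is affected, it is not the parameter that section 6.2 marks as main, and the study is exploratory (section 1.2.3).

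**What to change.** Add to 9.4 and 9.9, for example:

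*On-the-road lane departures will be expressed per analysed kilometre, using the unrounded analysed distance, and analysed with the mixed model of section 9.9. Drives without departures are kept as zero. For this endpoint, all analysable kilometres of a prematurely stopped drive of more than 20 km are used. The rate over the last 10 km is a sensitivity analysis.*

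The 10-km window can stay as it is for SDLP and the speed measures.

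The cost is a few lines of text and one derived variable. Speed and lateral position are already recorded continuously (section 7.1), so analysed distance can be obtained without new data. The 5-km rounding used to tabulate stopped tests is too coarse for this. Section 10.6.2 classes statistical analyses other than those described as non-substantial changes.

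Two downsides remain. A stopped drive's rate is less precise than that of a completed drive. Some upward bias also stays if departures rise just before the stop: at c = 2, with 4 of 24 stopped at 20 km, a true ratio of 2 becomes 2.17. If the rise is steep enough (c above 2.2 for stops at 20 km), the raw count is closer to the truth, so the distance at each stop and the last-10-km rate should be reported with the result.

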### 9.5 Analysis sets

Data of all subjects participating in the study will be included in the analyses if the data can meaningfully contribute to the objectives of the study.

#### 9.5.1 Safety set

The safety population will be defined as all subjects who were validated and received at least 1 study intervention.

#### 9.5.2 Pharmacodynamic analysis set

The analysis population for efficacy is defined as all subjects who were validated, received at least one intervention, and have at least one post-baseline assessment of the parameter being analysed.

## 9.6 Subject disposition

Subject disposition will be listed by subject.

The following subject data will be summarized:

- number and percentage of subjects screened,
- number and percentage of subjects enrolled,
- number and percentage of subjects completed or prematurely discontinued;
- number and percentage of subjects included in safety population;
- number of subjects included in the PS analysis population;
- number and percentage of subjects completed.

A subject who completed the study is defined as a subject where the last assessment is finished.

## 9.7 Baseline parameters and concomitant medications

### 9.7.1 Demographics and baseline variables

Continuous demographic variables (e.g., age, height, weight, BMI) will be summarized by descriptive statistics (n, mean, SD, median, Min, Max).

Qualitative demographic characteristics (sex, race/ethnicity) will be summarized by counts and percentages.

### 9.7.2 Medical history

Medical history will only be listed.

## 9.8 Safety and tolerability endpoints

The safety set is used to perform all safety analyses.

### 9.8.1 Adverse events

The AE coding dictionary for this study will be Medical Dictionary for Regulatory Activities (MedDRA). It will be used to summarize AEs by primary system organ class (SOC) and preferred term (PT).

All adverse events will be displayed in listings.

### 9.8.1 Prematurely discontinued on-the-road driving tests

Before and during the on-the-road driving test the subject and/or the driving instructor can stop the test prematurely for safety reasons. This will be noted as an event and the events will be summarized.

The number of subjects who did not finish the test will be summarized by:

1. Person who stopped the test (subject or driving instructor);
2. Amount of kilometres driven (rounded to 5km);

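### Stopped on-the-road drives are summarised without sleep state, so the listed summary does not show whether safety stops were more frequent after sleep deprivation

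*Protocol*

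**What the plan says.** The second of the two sections numbered 9.8.1 in the protocol deals with on-the-road drives that the subject or the driving instructor stops for safety, before or during the test. Each stop is recorded as an event, and the events are to be summarised. The section then fixes the form: "The number of subjects who did not finish the test will be summarized by" two classifiers, namely "Person who stopped the test (subject or driving instructor") and "Amount of kilometres driven (rounded to 5km"). No other classifier is listed.

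For pharmacodynamic endpoints, Section 9.9 does name the sleep state: "All PD endpoints will be summarised (n, mean, SD, SEM, median, Min and Max values) by group (sleep/sleep deprivation").

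Section 9.4 (Part A) decides what a stopped drive contributes to the driving analysis: "Prematurely stopped on-the-road tests will only be included if more than 20 kilometres is driven", and then only its last 10 km are analysed.

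Table 1 and Section 3.1 place a road drive at 9:00 and 14:00 in the well-rested period and at 9:00 in the sleep-deprived period. The drive at screening is for training only.

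**The concern.** Sleep state is the only experimental factor in this crossover, and Part A sets out to assess its effect on next-morning driving. A drive that the subject or instructor ends for safety bears directly on that objective. According to Section 7.2, the only safety assessments are the one made during the driving test and the observation of adverse events. Yet the summary that the protocol lists for stopped drives leaves out the factor under study.

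The counting unit adds to the difficulty. A count of subjects suits one drive per person, but here each person has three. A subject who stops twice may have two different stoppers and two distances, and the section does not say how that person is classified.

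The point also reaches the standard deviation of lateral position (SDLP), the main driving parameter. Stopped drives are either dropped or shortened in that analysis. If stops cluster in the deprived state, the drives lost or truncated would be those of the most affected subjects, and a reader would want to see that.

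**Working it through.** The protocol gives no expected number of stopped drives, so there is no stated figure to reproduce. The check is a count of drives at risk, followed by the splits that one pooled total allows.

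**Inputs**
- Part A subjects: 24 (Section 1.2.2).
- Rested road drives per subject: 2, morning and afternoon (Section 3.1, Table 1).
- Deprived road drives per subject: 1, morning (Section 3.1, Table 1).
- Classifiers for stopped drives: stopper and distance (Section 9.8.1).
- SDLP rule: more than 20 km needed, last 10 km used (Section 9.4), on a 55-km circuit (Section 7.1).

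**Step 1: drives at risk**
- Rested: 24 × 2 = 48.
- Deprived: 24 × 1 = 24.
- Total: 48 + 24 = 72, two thirds of them rested.

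**Step 2: what a pooled total allows**

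Take T stops, with k in the deprived state. The rates are k/24 deprived and (T − k)/48 rested. T is an assumption, shown over a range. For simplicity each stop belongs to a different subject.

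| Pooled stops T | All deprived | Equal rates | All rested |
|---|---|---|---|
| 3 | 3/24 = 12.5% vs 0/48 | 1/24 = 4.2% vs 2/48 = 4.2% | 0/24 vs 3/48 = 6.3% |
| 6 | 6/24 = 25% vs 0/48 | 2/24 = 8.3% vs 4/48 = 8.3% | 0/24 vs 6/48 = 12.5% |
| 9 | 9/24 = 37.5% vs 0/48 | 3/24 = 12.5% vs 6/48 = 12.5% | 0/24 vs 9/48 = 18.8% |

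Within a row the pooled total is the same. Stopper and distance do not separate the columns, because neither depends on knowing the state.

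**Step 3: the subject count**

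Six subjects who did not finish could account for 6 × 1 = 6 to 6 × 3 = 18 stopped drives, so the subject count does not fix the number of stops either.

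**Step 4: what Section 9.9 adds**

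The n per group for on-road SDLP shows how many values each state contributes. A drive stopped at 15 km and a recording lost for a technical reason both reduce n by one. A drive stopped at 30 km keeps n unchanged, although only 10 km of it is used where a completed drive covers the 55-km circuit. So net loss by state is visible, but safety stops and truncation by state are not.

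**Step 5: why session matters**

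Sections 3.1.2 and 9.9 compare the rested morning with the deprived morning and keep the rested afternoon for repeatability. A stop in the afternoon does not touch the main comparison; a stop in either morning does.

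**The case against.** The strongest reply is that Section 9.1 leaves full details of the displays to the SAP, which is not at hand, and that nothing in Section 9.8.1 forbids a column for sleep state. It is true that the SAP may add one. But Section 9.8.1 is not merely silent: it names a counting unit and lists two classifiers, and a SAP that follows it literally would leave state out. The general deferral does not repair a breakdown that the protocol has itself set.

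The section also says that the events will be summarised, so a count of events is foreseen besides the count of subjects. That stands and softens the complaint about the unit, but the only breakdown given is attached to subjects.

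The protocol has no safety objective, calls itself exploratory and names SDLP as the main parameter. That is fair, and it limits the weight of the point without removing it, since the stops also determine which drives enter the SDLP analysis and in what length.

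A reader might extend the point to adverse events, because the text there reads "It will be used to summarize AEs by primary system organ class (SOC) and preferred term (PT") and names no state. The documents do not support that. It is ordinary protocol wording, "All adverse events will be displayed in listings", and a split by state is detail normally left to the SAP.

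A reader might also infer that rounding to 5 km changes which drives are analysed. Nothing says that the 20 km rule uses rounded distances. What remains is presentational: if rounding is to the nearest 5 km, which the protocol does not state, drives of 18 km (excluded) and 22 km (kept) would both print as 20 km.

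**Conclusion.** The point holds for stopped on-the-road drives. As written, the summary pools 48 rested and 24 deprived planned drives and does not show whether safety stops differ by sleep state. With six stops, the deprived-state rate could lie anywhere from 0% to 25% for the same total. The drive counts assume that all 24 Part A subjects complete both periods; the totals of 3, 6 and 9 stops are illustrations, not expectations.

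Three stronger readings are tempting but not supported:
- **That the trial cannot show a difference.** The schedule fixes the state and session of each drive, so a table by state can be made. The gap lies in the summary that is specified.
- **That a table by state would show sleep deprivation caused the stops.** In this unblinded crossover it would give a descriptive comparison of frequencies, not attribution of single events.
- **That losses from the SDLP analysis are hidden.** Section 9.9 gives n by group, so net missing values are visible; only the reason and the truncation are not.

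This is an improvement in reporting at almost no cost. It does not affect sample size, power or the main analysis.

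**What to change.** In the Section 9.8.1 text on discontinued drives, make the drive the counting unit and tabulate as follows:

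1. Stopped drives and drives not started, each by sleep state and session (rested morning, rested afternoon, deprived morning), with the drives planned in each as denominator: 24, 24 and 24.
2. Within each of these, who stopped the drive (subject or instructor).
3. For each state, how many stopped drives covered 20 km or less (excluded from SDLP) and how many covered more than 20 km (last 10 km used), so that the table matches the Section 9.4 rule.

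Describe the comparison between states as descriptive. The number of subjects with at least one stopped drive can stay as an additional line.

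The cost is table layout only. State and session follow from the schedule, and stopper and distance are already needed for the present summary. No extra subjects, visits or assessments are required. Section 10.6.2 already treats statistical analyses other than those in the protocol as non-substantial changes.
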